### Aims of This Study

In this exploratory randomized controlled trial (RCT), we will evaluate whether an 8-week CBT-based intervention, delivered through ThinkNinja for Epilepsy (Healios Ltd), is a clinically effective tool for improving the quality of life, mental health, and emotional well-being in a large sample of people with epilepsy.

We hypothesize the following:

There will be an improvement in participants’ self-reported quality of life scores, as measured by the 10-item patient-weighted Quality of Life in Epilepsy questionnaire (QOLIE-10-P) [28], as a result of the ThinkNinja for Epilepsy intervention.There will be an improvement in participants’ self-reported anxiety, depression, impression of change, and medication adherence, as measured by the 7-item Generalized Anxiety Disorder assessment (GAD-7) [29], the 9-item Patient Health Questionnaire (PHQ-9) [30], the Patient Global Impression of Change questionnaire (PGIC) [31], and the Medication Adherence Questionnaire (MAQ) [32], respectively, as a result of the ThinkNinja for Epilepsy intervention.There will be a positive association between the level of engagement with the app and the primary and secondary outcomes.

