### Sample Size

A formal sample size calculation was based on assumptions of QOLIE-10-P means and SDs from earlier studies [37,38]. It was performed using a 2-tailed *t* test of equal means at a significance level of .05 and a power of 80% for an estimated medium effect size (Cohen *d*=0.5). All calculations were done using the software nQuery (version 7.0; Statsols) [39]. We intend to recruit 184 people—92 participants in each arm—so that we can accommodate a dropout rate of 30%.

The chi-square method was used to determine the power for structural equation modeling (SEM) [40] using the associated online power calculator [41]. It was determined that with a sample size of 184 (see above) and a *P* value of .05, the proposed 11-parameter SEM analysis would be powered at 0.705 (70.5%).

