In addition to this, a sensitivity analysis that uses both the primary and secondary outcomes will be performed. To explore both between-subjects (ie, arm A vs arm B) and within-subject (ie, T0 vs T1 vs T2 vs T3) differences, a series of repeated-measures (2 × 4) analyses of variance (ANOVAs) will be performed in the first instance with both the primary outcome measure (ie, QOLIE-10-P score) and the secondary outcome measures (ie, GAD-7, PHQ-9, PGIC, and MAQ scores) as dependent variables. All of these ANOVA tests will be powered at 0.80 (*P*=.05). The output from this series of ANOVAs will permit the necessary sensitivity analyses to be completed.

Further exploratory subgroup analyses will be performed for the following:

Change in primary and secondary outcomes for subgroups defined by baseline characteristics and demographics, such as age and gender.Change in primary and secondary outcomes stratified by app use, videoconference use, and text support use.Engagement variables: low versus high frequency and duration of app use.

Responder and nonresponder groups will be identified on the basis of changes in primary and secondary outcomes, and these groups will be characterized in terms of baseline characteristics, demographics, and app use variables. Descriptive statistics will be produced, and a regression model will be performed to identify variables associated with responder status. An SEM model will then be developed where baseline characteristics will be independent variables, app use and content variables will be mediating latent variables, and quality of life will be the dependent variable. Regression coefficients will be reported with 95% CIs. These analyses will be performed as an intention-to-treat analysis, using all randomized participants with imputation of missing end-of-study (T2) observations, with the exception of the sensitivity analyses, which will be per-protocol analyses.

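### The all-randomised, T2-imputed rule is applied to the engagement, responder and SEM analyses, where it protects no randomised comparison and gives a post-app outcome to people who may never have had the app

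*Protocol article*

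**What the plan says.** The third hypothesis (Aims of This Study) is: "There will be a positive association between the level of engagement with the app and the primary and secondary outcomes".

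Data Analysis addresses it in several ways. Outcomes are compared across levels of app, video and text-support use, and between low and high engagement. Then "Responder and nonresponder groups will be identified on the basis of changes in primary and secondary outcomes"; the groups are described by baseline and app-use variables, and a regression looks for correlates of responder status. Last comes an SEM in which app use and content mediate quality of life. The section closes by declaring these analyses intention-to-treat, "using all randomized participants with imputation of missing end-of-study (T2) observations". The one exception is the sensitivity analyses, which are per-protocol arm-by-time ANOVAs.

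Four other statements bear on this:
- **Outcomes and Variables:** T2 falls eight weeks after the participant starts the app.
- **Study Procedure:** arm B receives the app after eight weeks.
- **Study Design:** the within-subject analysis covers people who complete the programme, in either arm. The Abstract says that it includes everyone.
- **Sample Size:** "We intend to recruit 184 people—92 participants in each arm", "so that we can accommodate a dropout rate of 30" per cent. SEM power of 0.705 is calculated at 184.

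**The concern.** Intention-to-treat preserves the balance that randomisation gives to a comparison of arms. An association between outcome and app use is observational in any analysis set, so keeping everyone in brings no such benefit. It has a cost: outcome values must be created for people whose use may be low or zero, and those values help to set the slope under study.

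For part of arm B this follows from the design alone. Nobody lost during the wait can have used the app or answered a post-app questionnaire, yet the rule would classify that person as a responder or nonresponder to it.

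The planned sensitivity analyses would not reveal a problem. They compare arms over time without app use as a predictor, and for arm B the per-protocol cohort requires only T–1 and T0, not the post-app T2. The Conclusions section says the engagement analysis is meant to inform future research and app development, so a distorted slope would have consequences.

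**Working it through.** **1. The plan's own figure.** The calculation in Sample Size is stated as follows: "It was performed using a 2-tailed *t* test of equal means", with two-sided alpha 0.05, power 0.80 and d = 0.5. The normal approximation gives n = 2(1.960 + 0.842)²/0.5² = 62.8 per arm. The t-test solution is 63.77, rounded to 64. Then 64/(1 − 0.30) = 91.4, rounded to 92 per arm, or 184. The stated N reproduces.

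**2. How much would be imputed.** 0.30 × 184 = 55.2, so about 55 values imputed and 129 observed. In arm B, 0.30 × 92 = 27.6, so at most 28 people never reach the app, and only if every arm B dropout falls in the wait. The article does not split the 30% by arm or period.

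**3. The timeline.**
- Arm A: app at week 0, T2 at week 8.
- Arm B: app at week 8, T2 at 8 + 8 = week 16.
- Arm B, lost before week 8: zero use and no T2, but in the intention-to-treat cohort by allocation. T2 is imputed, a change score follows, and so does a responder status.

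If T2 were instead read as arm B's week-8 assessment, all 92 would have zero use by allocation. The all-randomised set would still be wrong for an engagement question.

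**4. Size of the possible distortion.** There is no closed formula, so this was simulated with 800 replicates. From the plan: N = 184, 30% missing T2, 24 sessions (8 weeks × 3). Assumed: sessions completed spread over 0 to 24; mean improvement 0.5 SD; SD of change near 1; slope in SD of change per 8 sessions; arm B members lost in the wait have zero use; other missingness ranked on low use with weight 0 (none), 0.5 (moderate) or 0.9 (strong). Multiple imputation (MI) used 20 sets and Rubin's rules. Cells show mean slope and rejection rate at 0.05.

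| True slope | Arm B lost in wait | Link to low use | Observed cases | MI with use | MI without use | No change from baseline |
|---|---|---|---|---|---|---|
| 0.30 | 0% | none | 0.299, 85% | 0.300, 86% | 0.208, 62% | 0.212, 82% |
| 0.30 | 15% | moderate | 0.299, 83% | 0.304, 82% | 0.159, 30% | 0.299, 99.5% |
| 0.30 | 15% | strong | 0.296, 69% | 0.293, 64% | 0.112, 6% | 0.345, 100% |
| 0.30 | 30% | moderate | 0.305, 85% | 0.298, 83% | 0.151, 31% | 0.305, 100% |
| 0 | 0% | none | −0.002, 5% | 0.001, 5% | 0.003, 1% | 0.004, 6% |
| 0 | 15% | moderate | 0.000, 6% | 0.001, 5% | −0.002, 0% | 0.114, 37% |
| 0 | 15% | strong | 0.000, 6% | −0.002, 5% | 0.000, 0% | 0.176, 78% |
| 0 | 30% | moderate | −0.002, 5% | −0.003, 5% | 0.002, 0% | 0.132, 55% |

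The Monte Carlo standard error of a 5% rate is √(0.05 × 0.95/800) = 0.8 percentage points.

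The no-change result depends on mean improvement. In a simpler simulation (normally distributed use, no arms, logistic missingness), its false-positive rate was 31–43% at a mean of 0.5 SD and 13–18% at 0.3 SD.

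**5. SEM power.** The article gives no degrees of freedom, so 0.705 could not be reproduced. As an illustration only, an RMSEA test of 0.05 against 0.08 gives 0.705 at N = 184 with 47 degrees of freedom, a value chosen to match. The same test at 129 observed gives about 0.52.

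**The case against.** The strongest reply is that the harm comes from imputation methods the article never names. It says only that missing T2 will be imputed. The model may be in an analysis plan that is not shown, so its absence is not a fault. With app use in the model, the simulated slope is 0.29 to 0.30 and false positives are about 5%. This stands. A reader might infer that the stated rule is worse than not imputing at all; the documents do not support that, because it holds only for use-blind or no-change imputation.

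Second, nothing in the article says that missing T2 goes with low use. Questionnaires are completed online on the study platform, and people lost to follow-up are pursued by text and email, so stopping the app does not by itself remove T2. This also stands. The link is plausible, since participants are asked to keep app notifications on so that the team can reach them, but it is an inference. Observed-case regression has its own condition: missingness must not depend on the unseen outcome once use is known.

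Third, Study Design speaks of completers, which would leave out people lost in the wait. But it conflicts with the closing rule in Data Analysis rather than overriding it, and the Abstract points the other way.

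Fourth, the trial and these subgroup analyses are labelled exploratory, and the primary comparison is untouched. That limits the weight of the point. It does not justify giving a responder status to someone who never had the treatment.

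**Conclusion.** The concern holds in a limited form. The article fixes an all-randomised, imputed set for questions about app use, where that set has no protective role. By design this gives a post-app outcome and a responder status to any arm B participant lost in the wait. Two sections disagree on who is included. None of this depends on an assumption about why T2 is missing.

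The size of any bias does. It requires missing T2 to track low use together with imputation that ignores use or assumes no change. Without that link no false association appeared (rejection at most 6%), and the worst result was dilution from 0.30 to 0.21. It would be tempting to conclude that imputation largely decides the engagement result. That goes too far: about 70% of T2 values would be observed at the planned dropout, and a suitable model leaves the slope where the observed cases put it. The simulation settings are assumptions, shown as a range. The point merits a change to the plan but does not threaten the primary analysis.

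**What to change.** - Limit the closing sentence of Data Analysis to the randomised comparison of arms, naming the 8-week value in each arm (T2 in arm A, T0 in arm B, as the per-protocol definition already does).
- Reconcile it with Study Design and the Abstract, so that one population is stated for the pooled analyses.
- Run the engagement, responder and SEM analyses on participants given app access. Use observed T2, with full-information maximum likelihood in the SEM, or multiple imputation whose model contains app use, arm, baseline and T1 scores. Show observed-case results beside any imputed ones.
- Assign no responder status to anyone never given the app.
- Restate SEM power at the N expected under this rule.

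The cost is wording and some programming, plus a smaller N. If 15% or 30% of arm B were lost in the wait, 184 − 14 = 170 or 184 − 28 = 156 people would remain before other missing T2 values. At the planned dropout about 129 would have observed T2.

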### Data Analysis

The analysis will be performed in two phases. The first phase of analysis will occur after completion of the 8-week (T2) outcome measures, when all participants in arm A have completed the 8-week program and can be compared to the waiting-list control participants (arm B). The second phase of analysis with the pooled data will occur after the completion of the 8-week follow-up period (T3) outcome measures for all participants.

The following patient cohorts will be used in the analysis:

The per-protocol study cohort will include all allocated participants with at least 80% completed questionnaire data, including a completed QOLIE-10-P score, at baseline (T0 ThinkNinja for Epilepsy group and T–1 wait-list group) and at 8 weeks (T2 ThinkNinja for Epilepsy group and T0 wait-list group).The intention-to-treat study cohort will include all allocated participants.

Available information on screened participants who were not randomized will be summarized.

Descriptive statistics will be produced for the distribution of all variables, including baseline demographic variables, app use, and engagement variables, as well as for each outcome variable at each time point. The change in each outcome from baseline will be reported in terms of mean and SD. An analysis of reliable and clinical change will be produced for the GAD-7 and PHQ-9 scores in order to determine the percentage of those who had clinical and reliable change (ie, clinical recovery) after taking part in the intervention.

The primary outcome analysis (ie, quality of life) will be performed for the overall cohort, both unadjusted and adjusted for baseline characteristics, app use, and app content variables. We will be comparing changes in quality of life (ie, QOLIE-10-P scores) from baseline to completion of the 8-week program.

The secondary outcome analysis will constitute analyzing the change in GAD-7 (ie, anxiety) and PHQ-9 (ie, depression) scores. In addition, we will be reporting on the results of the MAQ and PGIC, using descriptive statistics.

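### The per-protocol cohort does not guarantee the four visits that its repeated-measures ANOVA uses, so unless another rule is set, members with a missing visit would be lost from that sensitivity analysis

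*Protocol article*

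**What the plan says.** All of this is in the Data Analysis section of the protocol article unless stated otherwise.

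- **Cohort.** Per-protocol membership requires "at least 80% completed questionnaire data, including a completed QOLIE-10-P score, at baseline" and again at 8 weeks. Baseline is "T0 ThinkNinja for Epilepsy group and T–1 wait-list group"; the 8-week visit is "T2 ThinkNinja for Epilepsy group and T0 wait-list group".
- **Model.** For the sensitivity analysis, "a series of repeated-measures (2 × 4) analyses of variance (ANOVAs) will be performed", covering arm and "within-subject (ie, T0 vs T1 vs T2 vs T3) differences".
- **Missing data.** The listed analyses are by intention to treat with imputation of T2 only, "with the exception of the sensitivity analyses, which will be per-protocol analyses". No other imputation is named.
- **Timing.** Outcomes and Variables counts T1 and T2 from the start of the intervention (4 and 8 weeks) and puts T3 8 weeks after the active period ends. Study Procedure gives arm B the app after 8 weeks.
- **Dropout.** Sample Size sets 92 per arm "so that we can accommodate a dropout rate of 30" percent. It does not split that figure by arm or visit.

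**The concern.** The cohort is built for the randomised 8-week comparison, but the model assigned to it covers a different set of visits. A person in arm B who completes T–1 and T0 and then stops is a per-protocol member with three of the four ANOVA cells empty. A person in arm A who misses T1 or T3 is also a member with an incomplete row. A classical repeated-measures ANOVA cannot use an incomplete row, and the T2 imputation does not extend to this analysis.

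The result would then describe people who returned every form through T3, under the label of a larger cohort. Precision is lost because collected data go unused. The loss is also likely to be uneven, since arm B has more unguaranteed visits and a longer time to its last one.

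**Working it through.** **1. The plan's own sample size.** A two-sided t test with d = 0.5, alpha 0.05 and 80% power needs 64 per arm (power 0.801). Then 64 / 0.7 = 91.4, rounded up to 92 per arm, or 184 in total. This reproduces the plan and is not in dispute.

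**2. Guaranteed visits against ANOVA levels.**

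| Arm | Visits required for membership | Of these, ANOVA levels | Not guaranteed |
|---|---|---|---|
| A | T0, T2 | T0, T2 (2 of 4) | T1, T3 |
| B | T–1, T0 | T0 (1 of 4) | T1, T2, T3 |

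The guarantee is firm for the QOLIE-10-P only. The 80% rule does not ensure that each secondary scale is complete, even at the required visits.

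**3. Time to T3.** Arm A: 8 + 8 = 16 weeks, which is 8 weeks past its last guaranteed visit. Arm B: 8 + 8 + 8 = 24 weeks, which is 16 weeks past its last guaranteed visit. The Results section says arm B takes 16 weeks to complete the study. That conflicts with these definitions: 8 weeks of waiting plus 8 of program already make 16, leaving no time for T3, yet Data Analysis expects T3 for all participants. Figure 1, cited there, is not shown.

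**4. Members without all four visits.** The only dropout figure is 30%, so two readings are shown. Both assume a constant rate within each arm and that people who leave do not return.

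- *30% is the total loss by T3 in each arm.* Complete by T3: 92 × 0.7 = 64.4 in each arm. Cohort at week 8: arm A 92 × 0.7^(8/16) = 77.0; arm B 92 × 0.7^(8/24) = 81.7. Lost: 1 − 64.4/77.0 = 16% in A; 1 − 64.4/81.7 = 21% in B.
- *30% is lost in every 8 weeks.* Cohort: 92 × 0.7 = 64.4 in each arm. Complete by T3: arm A 92 × 0.7² = 45.1; arm B 92 × 0.7³ = 31.6. Lost: 30% in A; 51% in B.

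**5. Precision of the T0–T2 change, arms pooled.** Assumptions: unit variance and a correlation of 0.6 between any two visits, treated as known.

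- Complete cases: SE = √[2(1 − 0.6)/n].
- Likelihood analysis: add, over dropout patterns, (number with the pattern) × (inverse covariance of the visits they have). Invert the sum and take the variance of the T2 minus T0 contrast.

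Observed numbers at T0, T1, T2, T3:

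| Reading | Arm A | Arm B | SE, complete cases | SE, likelihood | Ratio |
|---|---|---|---|---|---|
| 30% total by T3 | 77.0, 77.0, 77.0, 64.4 | 81.7, 77.0, 72.5, 64.4 | √(0.8/128.8) = 0.0788 | 0.0726 | 1.09 |
| 30% per 8 weeks | 64.4, 64.4, 64.4, 45.1 | 64.4, 53.9, 45.1, 31.6 | √(0.8/76.6) = 0.1022 | 0.0838 | 1.22 |

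Arm A gives a direct check. All its members have T0 and T2, so its ratio is √(77.0/64.4) = 1.09 under the first reading and √(64.4/45.1) = 1.20 under the second.

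**The case against.** The visit counts are not contestable, but several inferences from them are.

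- **Listwise deletion is not stated.** It follows from the named method with no imputation assigned to it. An analysis plan that is not shown could set another rule, so the point has to be conditional. It is still more than omitted detail: the article itself fixes the model, its four levels, the cohort by arm and visit, and the scope of imputation, and these do not fit together.
- **The larger loss figures extrapolate.** A reader might infer that half of arm B's cohort will be lost. That needs the single 30% figure to recur every 8 weeks; read as a total, it gives 21%.
- **The imbalance between arms is conditional.** It holds under similar attrition rates, but no arm-specific rate is given.
- **Bias is not shown.** A reader might infer that completers are doing better and that improvement is therefore overstated. The documents say nothing about why people leave. In simulations where poorer scores were assumed to raise dropout, a true gain of 0.50 SD was estimated at 0.52 to 0.58; under a different dropout pattern the bias was almost nil.
- **The consequence is limited.** This is a sensitivity analysis in a trial described as exploratory. The primary analysis is by intention to treat with T2 imputation.

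All five objections stand as limits on the claim. None removes the mismatch between cohort and model.

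**Conclusion.** The point holds as a mismatch between a stated cohort and a stated method. Membership secures two of the four ANOVA visits in arm A and one in arm B, with no imputation assigned to the analysis. Unless another rule is set, the ANOVA would rest on a smaller group than the cohort it is said to describe.

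The inflation of the standard error ranges from about 9% to about 22% over the two dropout readings, given a correlation of 0.6 and dropout without return. A larger loss in arm B further assumes similar attrition in both arms and the 24-week timing that the visit definitions imply. The documents do not support a claim of bias in either direction, nor any effect on the primary analysis. The change is worth making because it is cheap, but the trial's main conclusion does not depend on it.

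**What to change.** Replace the repeated-measures ANOVAs with a likelihood-based linear mixed model for repeated measures, with visit as a factor and an unstructured covariance, using every observed visit of the per-protocol cohort. Members with a missing T1, T2 or T3 then contribute the visits they have.

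The cohort does not need redefining. Requiring T0 plus at least one later visit, for example, would exclude the arm B member who stops after T0 and would drop the 8-week requirement in arm A.

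Separately, reconcile the 16 weeks given for arm B in the Results section with the 24 weeks implied by Outcomes and Variables and Study Procedure.

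The cost is analysis-plan wording and a different model call, with no new data. The one downside is that results are reported as model contrasts instead of ANOVA F tests.

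### All sensitivity analyses are confined to participants with a completed 8-week QOLIE-10-P, so none can vary what is assumed about participants whose primary outcome is imputed

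*Protocol article*

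**What the plan says.** The Data Analysis section of the protocol article names two cohorts. The intention-to-treat cohort is everyone allocated. The other is set by data completeness: "The per-protocol study cohort will include all allocated participants with at least 80% completed questionnaire data, including a completed QOLIE-10-P score, at baseline" and again at 8 weeks. The 8-week comparison is T0 to T2 in arm A against T–1 to T0 in arm B.

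The section ends by stating that the analyses are intention-to-treat, with missing T2 values imputed, "with the exception of the sensitivity analyses, which will be per-protocol analyses". The imputation method is not given. The only sensitivity analysis described is a series of 2 × 4 repeated-measures ANOVAs (arm by T0, T1, T2, T3) on the primary and secondary outcomes.

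The Sample Size section sets recruitment at 184, "92 participants in each arm", to allow for 30% dropout.

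**The concern.** When a primary outcome is imputed, the result depends partly on an assumption about unobserved values. A sensitivity analysis aimed at that dependence keeps the affected participants and changes the assumption. Here the affected participants are removed by the definition of the cohort, so nothing assumed about them can alter any sensitivity result.

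This matters because informative dropout is plausible on the plan's own terms. The trial is open, outcomes are self-reported, the control is a wait-list, and one hypothesis is that engagement with the app goes with better outcomes. If arm A participants who find the app unhelpful also stop answering, the effect in all allocated participants may be smaller than in those who answer. No stated analysis would explore by how much.

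**Working it through.** **1. Reproduce the planned sample size.** Inputs from Sample Size: two-sided *t* test at .05, "a power of 80% for an estimated medium effect size", *d* = 0.5, 30% dropout.
- The two-sample *t* test (noncentral *t*) needs 64 per arm, which gives power 0.801.
- Inflation: 64 / 0.70 = 91.4, rounded up to 92 per arm, 184 in total.

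This matches the plan exactly, so 30% is a real planning input. The normal approximation gives 63, then 90 per arm, 180 in total.

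**2. Who is outside the sensitivity analyses.** At 30% dropout, 92 × 0.30 = 27.6, about 28 per arm, and 184 × 0.30 = 55.2, about 55 overall. About 64 per arm remain. This reads the imputation clause as covering the 8-week comparison point in both arms, which is T2 in arm A and T0 in arm B.

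**3. What the described sensitivity analysis compares.**

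| | Randomised 8-week contrast | 2 × 4 ANOVA |
|---|---|---|
| Arm A | T0 to T2 | T0, T1, T2, T3 |
| Arm B | T–1 to T0 (waiting) | T0, T1, T2, T3 (from app start onwards) |

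Arm B's T–1 is not in the ANOVA, and from T0 onwards both arms have the app. The model therefore compares immediate with delayed users over the same app period, not app with waiting list.

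**4. Illustration of what is left unexamined.** Work in SD units. Assume that completers differ by 0.5, that arm B dropout is uninformative, and that missing-at-random imputation without informative auxiliary data reproduces about 0.5. If missing arm A outcomes are worse than imputed by δ and the arm A dropout proportion is p:

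effect in all randomised = 0.5 − p × δ

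If arm A dropouts gain nothing over the wait-list, δ = 0.5:

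| Dropout p | Effect in all randomised | Completer effect |
|---|---|---|
| 10% | 0.5 − 0.10 × 0.5 = 0.45 | 0.5 |
| 20% | 0.5 − 0.20 × 0.5 = 0.40 | 0.5 |
| 30% | 0.5 − 0.30 × 0.5 = 0.35 | 0.5 |

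At 30% dropout, δ = 0.25 gives 0.425 and δ = 1.0 gives 0.20.

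**5. Tipping point, at 30% dropout with the completer standard error held fixed.**
- SE = √(2/64) = 0.177.
- Significance limit = 1.96 × 0.177 = 0.346.
- δ at the limit = (0.5 − 0.346) / 0.30 = 0.51.

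Using 64.4 completers per arm and a critical value of 1.98 gives SE 0.176, limit 0.349 and δ = 0.50. A shift of about 0.5 SD is enough either way.

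**The case against.** **This belongs in the analysis plan.** The choice of imputation method does, and its absence from a condensed article is no fault. But the article is not silent on the cohort for sensitivity analyses. It assigns them all to the per-protocol cohort, and an analysis plan that added one in all randomised participants would contradict that clause.

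**The protocol claims no robustness to missing data.** Correct. A reader might infer from the label that the per-protocol analysis is offered as such a check, but the article says only that the ANOVAs explore between- and within-subject differences.

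**The sensitivity analysis would confirm an inflated effect.** A reader might infer that it would return about 0.5 when the truth is 0.35, an overstatement of 43% (0.5 / 0.35 = 1.43). The documents do not support this. The described ANOVA does not estimate the randomised 8-week contrast, so it can neither confirm nor refute its size.

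**The imputed and completer results need not agree.** This stands. App use, T1 outcomes and, during the intervention, weekly measures are recorded. An imputation model using them could pull the intention-to-treat result away from the completer result, as could a conservative single imputation. It cannot be said that comparing the two is always uninformative. It remains true that the per-protocol analyses do not vary the imputation assumption.

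**The numbers are one-sided.** They are. Stopping the app is not the same as not answering questionnaires, non-responders are pursued by text and email, and 30% is an allowance rather than a forecast.

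**The wording is open on two points.** The sentence on intention-to-treat follows the responder and structural equation models and could be read as covering only those. The contrast it draws with the sensitivity analyses, and the use of the overall cohort for the primary outcome, favour the wider reading. On the narrow reading the sensitivity analyses are still per-protocol only. The cohort also requires 80% of questionnaire data, not all of it, but the QOLIE-10-P itself must be complete at both points.

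**Conclusion.** The point holds in a limited form. The stated clause places every participant with an imputed 8-week QOLIE-10-P outside every sensitivity analysis, up to about 55 of 184 at the planned dropout. In addition, the one analysis described does not address the randomised 8-week contrast. Both follow from the text without any assumption about dropout.

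The size of any bias does not follow from the text. The 0.35 to 0.45 SD range and the tipping shift of about 0.5 SD depend on a completer effect equal to the design value, no benefit in arm A dropouts, uninformative dropout in arm B, and missing-at-random imputation without informative auxiliary data. They show that the unexamined assumption could matter, not that the result will be overstated. The change should be made. It is not a reason to doubt the design as a whole, particularly in a trial described as exploratory.

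**What to change.** Amend the closing clause of the Data Analysis section so that at least one sensitivity analysis of the primary contrast (T0 to T2 in arm A against T–1 to T0 in arm B) is done in all randomised participants and departs from the main imputation assumption. Suitable choices are delta-adjusted multiple imputation carried to a tipping point, or reference-based multiple imputation with arm A's missing values drawn from the wait-list distribution. The details can sit in the analysis plan. Keep the per-protocol analysis as supplementary, and do not present it as a check on missing data.

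The cost is a change of wording and a few extra analyses, with no new data. The drawback for the sponsor is that the primary result may look less robust.
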